## Abstract

**Introduction:**

Aerobic and resistance training can effectively improve clinical management in people with type 2 diabetes (T2D). Low vitamin D (VitD) levels are associated with T2D risk and metabolic disturbances, and may help reduce this risk, particularly in individuals with low VitD levels. In this line, many individuals with T2D, who may also be older adults or have osteoporosis, regularly include VitD treatment in their healthcare routines. Although the impact of exercise has been extensively studied, its effect on diabetic patients taking VitD remains limited. The aim of this study is to investigate the effect of aerobic and resistance training on clinical parameters in patients with T2D already taking VitD.

**Discussion:**

Expected improvements in insulin resistance, glycated hemoglobin, lipid profile, and inflammatory markers are anticipated following a 16-week regimen of exercise in patients with T2D on VitD.

**Clinical trial registration:**

The study was registered on September 21, 2024, with the identifier number NCT06081387, https://clinicaltrials.gov/study/NCT06081387.

## Introduction

1

Type 2 diabetes (T2D) is a chronic disease characterized by insulin resistance and impaired pancreatic insulin production. The rapid growth of this epidemic reflects socioeconomic trends, including, among others, low levels of physical activity (PA) (1). In this regard, obesity and lack of regular exercise or a sedentary lifestyle are major causes of chronic disease and global mortality, in which PA plays a very significant role (2).

Low cardiorespiratory fitness (CRF) is a well-known risk factor and an important predictor of mortality for chronic diseases including T2D and obesity (3, 4). Aerobic and resistance training is the most effective way to increase CRF, and people with T2D clearly respond to training with this adaptation (5). Aerobic exercise interventions have shown to improve glycemic parameters, VO2 max and cardiac output in T2D, which was associated with a significant reduction in the risk of cardiovascular and mortality (5–7). Other studies have shown improvements of 10 to 15% in strength, bone mineral density, blood pressure, lipid profiles, cardiovascular health, insulin sensitivity, abdominal fat and muscle mass (6). Additionally, due to the increased prevalence of T2D with age and the age-related loss of muscle mass, known as sarcopenia, resistance training may have additional health benefits for older adults (8). As a result, PA has been established as an important therapy in the prevention, management, and treatment of T2D and its associated complications (9, 10).

Vitamin D (VitD) is a fat-soluble vitamin innately present in some foods. VitD promotes intestinal calcium absorption, maintains adequate serum calcium and phosphate concentrations to afford normal bone mineralization, and prevents hypocalcemic tetany (11). Together with calcium, VitD also helps protect older adults from osteoporosis. VitD has other physiological functions, including reducing inflammation and modulating processes such as cell growth, neuromuscular and immune function, and glucose metabolism (11). Thus, it is widely acknowledged that a significant portion of individuals with T2D, which may also present with advanced age, or osteoporosis, routinely integrate a VitD treatment into their healthcare routines (12). Low blood levels of VitD have emerged as a risk factor for TD2; it is often associated with metabolic alterations, such as an increased risk of glucose intolerance (13). Further, obesity is inversely correlated with VitD status, which can be attributed to the sequestration of soluble vitamins by adipose tissue (14). Furthermore, it has been found that low VitD levels are associated with insulin resistance and insulin secretion disorders leading to the development of TD2 (15). Therefore, VitD may play a functional role in glucose tolerance through its effects on insulin secretion and insulin sensitivity (16). In this line, several studies have hypothesized that VitD supplementation is a potential intervention to reduce the risk of T2D. In addition, other studies have shown that VitD is beneficial for people with pre-diabetes (17). However, VitD supplementation alone as an intervention cannot improve insulin sensitivity or glycemic control in an overweight population with previously normal VitD levels (18). Likewise, VitD supplementation also fails to improve glucose tolerance or pancreatic beta-cell function in patients with pre-diabetes.

Few studies evaluated the effects of VitD and PA in patients with T2D. Kim et al. showed that the combination had positive effects on abdominal fat and blood lipid profiles, but the metabolic characterization of these patients was limited, and results were inconclusive (19). Dadrass et al. showed that VitD supplementation, in addition to resistance training, had positive effects on some inflammatory markers (interleukin 6, tumor necrosis factor *α* and C-reactive protein) in men with T2D and VitD insufficiency but they did not analyze any non-inflammatory metabolic parameters (20). In conclusion, although some studies link VitD and aerobic or endurance exercise to improved T2D outcomes, the analyses are scattered and inconsistent, with incomplete metabolic characterization, low numbers of patients, and generally unreliable conclusions.

To overcome these limitations, the DIAVITEX study employs a randomized factorial design with a larger sample size and stratification by VitD treatment status, allowing the independent and combined effects of exercise and VitD to be assessed. It also incorporates a comprehensive metabolic characterization (including insulin resistance, glycemic, lipid, and inflammatory biomarkers) and a 16-week structured, supervised exercise program to ensure adherence and reproducibility. Involving pharmacists and primary care professionals further enhances safety and translational applicability in real-world clinical settings.

The DIAVITEX study aims to identify the effect of aerobic and resistance training in T2D patients on a VitD regime and to compare them with patients not exercising or not on VitD therapy, in order to provide evidence for optimizing disease management. The specific objectives are to evaluate the effect of aerobic and resistance training, with or without VitD treatment, on:

Insulin resistance (primary endpoint: HOMA-IR).Glycemic, lipid, inflammatory and renal biomarkers.Anthropometric measures.Adherence to the Mediterranean diet.Psychological well-being among patients with T2D before and after the intervention.The role of the pharmacist in patient follow-up including medication monitoring, intervention support, and safety oversight during the trial (exploratory process outcome).

We hypothesize that the combination of aerobic and resistance training with ongoing VitD treatment will lead to greater improvements in insulin resistance (primary endpoint: HOMA-IR) compared with exercise alone, VitD alone, or control (no intervention). Secondary hypotheses are that exercise, with or without VitD, will also improve glycemic control, lipid profile, body composition, inflammatory markers, diet adherence, and psychological well-being.

## Methods and analysis

2

### Study design

2.1

The DIAVITEX study is a randomized controlled clinical trial involving medicinal products, designed in accordance with Real Decreto 957/2020 of November 3rd, which regulates observational studies with human-use medicinal products. The trial framework is superiority, designed to test whether the combination of aerobic and resistance training with ongoing VitD treatment is superior to either intervention alone or control in improving insulin resistance.

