The sample size for this study was determined using the GRANMO program with the model of observed proportions with respect to a reference. For the calculation, it has been taken into account that the insulin resistance is the key to calculating the effects of aerobic and resistance training on clinical parameters in patients with T2D. The calculation has been made accepting an 𝜶 risk of 0.05 and a beta risk of less than 0.2 in a two-sided contrast. Based on preliminary data, there is a difference of HOMA-IR of -0.14% after 12 weeks of intervention (21). Although modest, this effect size has been reported as clinically relevant in previous clinical trials (22–24). It is assumed that the proportion in the reference group is 0.0139 (5.3 million people in Spain) (25). The percentage of necessary replacements has been predicted to be 20%. The present study is designed as an exploratory factorial randomized clinical trial; while not powered for a definitive test of interaction effects, the chosen sample size allows us to detect main effects with adequate power while providing preliminary evidence of potential interactions.

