### Statistical analysis

2.11

All data will be reported as mean and standard deviation. Data normality and homogeneity of variance will be tested using Shapiro–Wilk and Levens tests, respectively. The primary endpoint (change in HOMA-IR) from baseline to 16 weeks, will be analyzed using ANCOVA with group as the fixed factor, baseline HOMA-IR as covariate, and VitD treatment status included as a stratification variable. Secondary continuous outcomes (glycemic, lipid, inflammatory, anthropometric, dietary, and psychological well-being measures) will also be analyzed with ANCOVA, adjusting for baseline values. Categorical outcomes (e.g., adverse events) will be compared using χ^2^ or Fisher’s exact test. Bonferroni *post hoc* test will be used if there is a significant difference between the groups. Exploratory analyses will test for interaction effects between exercise and VitD status using factorial ANOVA models; these analyses are considered hypothesis-generating due to sample size limitations. In addition, exploratory analyses will be performed to examine potential sex-related differences in primary and secondary outcomes. Sex will also be included as a covariate in the statistical models when appropriate. Statistical power will be calculated by *post hoc* power analysis method by using G Power software.

The results will be analyzed using SPSS (version 22) for Windows. The significant level (*α*) of all statistical analyses will be 0.05.

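### The three-comparator superiority claim on HOMA-IR does not say that all three contrasts must succeed, and the omnibus-plus-Bonferroni step is valid for that claim but needlessly conservative

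*Protocol article*

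**What the plan says.** The protocol article states the claim twice. Study design (2.1) says the trial is "designed to test whether the combination of aerobic and resistance training with ongoing VitD treatment is superior to either intervention alone or control"; the outcome meant there is insulin resistance. The hypothesis in the Introduction expects greater improvement in HOMA-IR from the combination, "compared with exercise alone, VitD alone, or control (no intervention").

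Statistical analysis (2.11) gives the procedure. The primary endpoint "will be analyzed using ANCOVA with group as the fixed factor, baseline HOMA-IR as covariate, and VitD treatment status included as a stratification variable". The Bonferroni post hoc "test will be used if there is a significant difference between the groups". The significance level "of all statistical analyses will be 0.05". The exercise-by-VitD interaction is exploratory.

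The sample-size text under Participants (2.2) calls the trial exploratory and says it is sized for main effects. The same section explains that participants are stratified by existing VitD treatment and randomised to exercise or no exercise within strata.

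**The concern.** A claim of superiority to three comparators needs a rule for combining three contrasts: Group 1 vs 2, 1 vs 3 and 1 vs 4. The article states a specific claim and a specific test, and the two do not fit well. A significant omnibus test says only that some groups differ. Bonferroni pairs give separate pairwise statements. Neither says when the combination as such has succeeded.

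Two things are at stake:

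- **Power.** If all three contrasts must be significant, dividing alpha among them is not needed to control the error rate of the joint claim, and it makes a demanding claim harder still.
- **Interpretation.** If the rule is settled after the data are seen, a single significant pair could be presented as superiority of the combination. Group 1 vs 4 can be significant through exercise alone.

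**Working it through.** **Inputs.** Four groups of 20 (Table 1); 16 per group if the 20% replacement figure in 2.2 is taken as loss (20 × 0.8). Alpha is 0.05 two-sided. The Bonferroni divisor is not stated: 6 covers all pairs, 3 covers the Group 1 contrasts.

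**The plan's own figure.** No power is given for the three contrasts. The sample-size inputs cannot supply an effect size either: the text says "there is a difference of HOMA-IR of -0.14% after 12 weeks of intervention" and gives no SD. Entered as written (reference proportion 0.0139, change −0.0014, "risk of 0.05 and a beta risk of less than 0.2 in a two-sided contrast"), they give

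n = (1.960·√(0.0139·0.9861) + 0.842·√(0.0125·0.9875))² / 0.0014² ≈ 53,220,

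or 53,220 / 0.8 = 66,525 after dropout, not 80. That is a separate matter and nothing below depends on it. Effects are therefore assumed, in residual-SD units.

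**Error rate of the joint claim.** If the combination fails to beat at least one comparator, the chance that all three contrasts are significant in its favour cannot exceed the chance that this one contrast is. That chance is at most:

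- 0.05/2 = 2.5% without adjustment
- 0.025/3 = 0.83% with three-contrast Bonferroni
- 0.025/6 = 0.42% with six-pair Bonferroni

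All are valid; the last two are stricter than a 0.05 two-sided test requires.

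**Power by hand.** Take additive effects of d per component, so that Group 1 exceeds Groups 2 and 3 by d and Group 4 by 2d. For n = 20 and d = 0.8, the non-centrality of 1 vs 2 (and of 1 vs 3) is 0.8·√(20/2) = 2.53. On 76 df the critical values are 1.992 (0.05), 2.448 (0.05/3) and 2.709 (0.05/6). Approximate power for one contrast is Φ(2.53 − 1.992) ≈ 70%, Φ(2.53 − 2.448) ≈ 53% and Φ(2.53 − 2.709) ≈ 43%. Group 1 vs 4 has twice the non-centrality and rarely fails. Joint power therefore lies between the square of these values and the values themselves, because the contrasts share Group 1 and are positively correlated.

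**Power by simulation.** Normal outcomes, pooled variance, omnibus F at 0.05, then all three contrasts significant in the favourable direction. Repeat runs agree to about one percentage point.

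| n per group | d (SD) | Bonferroni, 6 pairs | Bonferroni, 3 contrasts | 0.05 each |
|---|---|---|---|---|
| 20 | 0.8 | 27–28% | 37–38% | 56–57% |
| 20 | 1.0 | 53–54% | 64% | 80% |
| 16 | 0.8 | 18–19% | 26–27% | 45% |
| 16 | 1.0 | 38–39% | 49% | 68–69% |

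The omnibus gate itself costs about one point or less under an all-three rule, so the loss comes from Bonferroni.

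**What an any-pair reading would do.** Suppose exercise works and VitD adds nothing, so Group 1 equals Group 2. With n = 20, omnibus test and six-pair Bonferroni, at least one Group 1 contrast is significant in 22%, 59%, 82% and 94% of trials at exercise effects of 0.5, 0.8, 1.0 and 1.2 SD. All three at 0.05 each are significant in at most about 2.5%.

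**Non-randomised contrasts.** The 2.5% bound assumes that VitD users and non-users would otherwise change equally. With an assumed stratum difference in HOMA-IR change of 0.3 or 0.5 SD favouring users, no VitD effect, and exercise effects of 0.8 to 1.0 SD (n = 20), the unadjusted all-three rule is met in about 14–15% or 30–33% of trials.

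**The case against.** **This is analysis-plan detail.** Success rules and the Bonferroni divisor are commonly left to an analysis plan, and this is a condensed article. That stands for the divisor. It does not dispose of the point, because the article itself states both the three-comparator claim and the procedure, and the procedure is poorly matched to the claim.

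**Nobody adopts an any-pair rule.** This stands. The ordinary sense of the wording is better than each, and the Discussion speaks of benefit beyond either intervention alone. A reader might infer that the plan would produce false combination claims in 22–94% of trials. The documents do not support that: no section says one pair suffices. In that scenario Group 1 truly differs from Groups 3 and 4, so those tests are not false rejections. The error would lie only in the step from one pair to the combination.

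**Bonferroni is not an error.** This also stands. A reader might call it the wrong correction, but it is valid for the joint claim and protects the separate pairwise statements. What remains is a loss of power.

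**An unadjusted all-three rule leans on confounded contrasts.** This stands and shapes the fix. Only exercise is randomised, and VitD users are treated for osteoporosis, osteopenia or deficiency. Dropping Bonferroni lowers the bar that a stratum difference has to cross.

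**The trial is exploratory and sized for main effects.** This lowers the weight of the point but does not remove it, since 2.1 declares a superiority framework for the combination.

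**Conclusion.** The concern holds as a mismatch between claim and procedure, not as an error-rate fault. The primary claim most naturally requires Group 1 to beat each of three comparators, but the text does not fix this. The stated procedure is conservative for that claim. At 20 per group and 0.8 SD per component, six-pair Bonferroni roughly halves the power (27–28% against 56–57%), and three-contrast Bonferroni costs about 19 points. At 1.0 SD the losses are about 27 and 16 points.

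The sizes rest on assumed standardised, additive effects, equal variances and normal outcomes, with baseline adjustment entering only through the residual SD. The protocol gives no SD against which to check them.

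The loose wording is a secondary risk: it permits, but does not prescribe, presenting a single pair as superiority of the combination. Nor would meeting all three contrasts prove that VitD adds benefit, because VitD use is not randomised. It is worth settling before outcome data are seen.

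**What to change.** In 2.1 and 2.11:

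- Replace the either/or phrase with *each of exercise alone, VitD alone and control*, and align the Introduction hypothesis.
- State that the joint claim on HOMA-IR requires Group 1 to improve more than Group 2, Group 3 and Group 4, each at two-sided 0.05 in the baseline-adjusted model, without Bonferroni.
- Keep Bonferroni for separate pairwise claims and state its divisor.
- Report Group 1 vs 3, when it stands alone, as the randomised effect of exercise among VitD users.
- Report Group 1 vs 2 and 1 vs 4, and any joint conclusion resting on them, as non-randomised comparisons and not as proof that VitD adds benefit.

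When the contrasts are written down, note that the four-level group factor already determines VitD status, so the model cannot estimate both terms as listed.

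The cost is a few sentences and no extra data. The downside is that the combination claim is harder to win than under an any-pair reading.

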### Participants

2.2

The study will include a total of 80 individuals of both sexes (female, male) with a diagnosis of T2D. Among them, 40 individuals will be required to be on a VitD treatment for at least, 6 months, for reasons recommended by the ECAP working group (including osteoporosis, osteopenia, and VitD deficiency), and the other 40 will not be receiving VitD supplementation.

Subjects will be recruited during usual medical care in a convenience-based by the collaborating physician from the Primary Care Center (CAP) Sant Rafael in Barcelona, Spain.

During the initial visit with the physician at CAP Sant Rafael, participants will be provided with the Patient Information Sheet and the Informed Consent and subsequently will be asked to provide their preferred contact information (phone number or email). This information will be used by the principal investigators from Blanquerna to reach out explaining the study with detailed instructions (explaining the patient information sheet and address any questions they may have). After receiving the information and clarifying any potential concerns, participants will be asked to sign the informed consent.

After enrollment and stratification by VitD treatment status, participants will be randomized within each stratum to exercise intervention or to no exercise. An independent investigator, not involved in recruitment or outcome assessment, will generate the randomization sequence using a computer-based block randomization method within VitD strata. Allocation will be implemented via a secure, web-based central randomization system accessible only after completion of baseline assessments and confirmation of eligibility. This ensures that the four groups (see Table 1) are balanced and clearly defined as: Group 1, Exercise + VitD users; Group 2, Exercise + VitD non-users; Group 3, VitD only (no exercise); and Group 4, Control (no VitD & no exercise).

**Table 1 tab1:** Group allocation of participants with T2D.

Group	VitD treatment status	Exercise intervention	*n*
1	On VitD ≥ 6 months	Exercise program	20
2	No Vit D treatment	Exercise program	20
3	On VitD ≥ 6 months	No exercise	20
4 (Con)	No Vit D treatment	No exercise	20

The sample size for this study was determined using the GRANMO program with the model of observed proportions with respect to a reference. For the calculation, it has been taken into account that the insulin resistance is the key to calculating the effects of aerobic and resistance training on clinical parameters in patients with T2D. The calculation has been made accepting an 𝜶 risk of 0.05 and a beta risk of less than 0.2 in a two-sided contrast. Based on preliminary data, there is a difference of HOMA-IR of -0.14% after 12 weeks of intervention (21). Although modest, this effect size has been reported as clinically relevant in previous clinical trials (22–24). It is assumed that the proportion in the reference group is 0.0139 (5.3 million people in Spain) (25). The percentage of necessary replacements has been predicted to be 20%. The present study is designed as an exploratory factorial randomized clinical trial; while not powered for a definitive test of interaction effects, the chosen sample size allows us to detect main effects with adequate power while providing preliminary evidence of potential interactions.

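### The sample size comes from a one-sample proportion model although the primary endpoint is a continuous between-group change in HOMA-IR, so the claim of adequate power for main effects is unsupported

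*Protocol article*

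**What the plan says.** All statements are in the protocol article.

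- **Model (section 2.2 Participants):** "The sample size for this study was determined using the GRANMO program with the model of observed proportions with respect to a reference".
- **Error rates (2.2):** "risk of 0.05 and a beta risk of less than 0.2 in a two-sided contrast".
- **Effect (2.2):** "there is a difference of HOMA-IR of -0.14% after 12 weeks of intervention".
- **Reference value (2.2):** "It is assumed that the proportion in the reference group is 0.0139 (5.3 million people in Spain").
- **Loss (2.2):** "The percentage of necessary replacements has been predicted to be 20" per cent.
- **Claim (2.2):** the trial is called exploratory and not powered for interaction, but "the chosen sample size allows us to detect main effects with adequate power".
- **Design (2.2, Table 1):** 80 people with type 2 diabetes, four groups of 20. Randomisation to exercise or no exercise takes place within vitamin D strata.
- **Endpoint (2.4.1) and analysis (2.11):** change in HOMA-IR from baseline to week 16, by ANCOVA with group as factor and baseline HOMA-IR as covariate.
- **Hypothesis (Introduction and 2.1):** the combination is superior to exercise alone, vitamin D alone and control.
- **After the trial (2.11):** power is to be calculated post hoc ("power analysis method by using G Power software").

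**The concern.** The calculation answers a different question from the one the trial asks. It tests whether a single observed proportion differs from a known value. The trial compares mean changes in a continuous index between randomised groups. The article defines no HOMA-IR responder, so no proportion of participants is available to be tested. The reference value is tied to a count of people in Spain, although every participant has type 2 diabetes. The calculation contains no between-group difference and no measure of HOMA-IR variability.

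Readers are nevertheless told that beta is below 0.2 and that main effects can be detected. If the trial finds no significant effect, that statement invites them to take the result as evidence that exercise does not change insulin resistance. This is the only sample-size justification in the article.

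**Working it through.** **Step 1. Reproduce the printed calculation.** Inputs from section 2.2: p0 = 0.0139, two-sided alpha 0.05 (z = 1.96), power 80% (z = 0.8416), loss 20%. The one-sample formula is

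n = [1.96·√(p0(1−p0)) + 0.8416·√(p1(1−p1))]² / (p1−p0)², then n/0.8 for loss.

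| Reading of the effect | p0 → p1 | n | after 20% loss |
|---|---|---|---|
| Fall of 0.14 percentage points | 0.0139 → 0.0125 | 53,220 | 66,525 |
| Fall of 0.14 | 0.0139 → −0.126 | impossible | – |
| Rise of 14 percentage points | 0.0139 → 0.1539 | 14.5, i.e. 15 | 19 |
| Rise of 14 points, reference 0.139 | 0.139 → 0.279 | 56.8, i.e. 57 | 71.1, i.e. 72 |
| The same by the arcsine formula | 0.139 → 0.279 | 64.5, i.e. 65 | 80.6, i.e. 81 |

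For the first row: (1.96 × 0.11708 + 0.8416 × 0.11110)² / 0.0014² = 0.10431 / 0.00000196 = 53,220. Other formula variants on this reading run from 38,937 to 73,482 before loss.

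A figure near 20 per arm therefore appears only if the effect is read as a rise of 14 percentage points. A figure near 80 needs that reading, a changed reference and the arcsine formula. Both contradict the printed sign and unit.

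**Step 2. Check the reference value.** 5.3 million / 0.0139 = 381 million. 5.3 million / 0.139 = 38 million. A slipped decimal is possible, but correcting it does not make the model suit the endpoint.

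**Step 3. What the actual comparison would give.** Two-sample t-test, two-sided alpha 0.05. The article gives no SD of change and no baseline HOMA-IR, so SDs of 0.5, 1 and 2 units and a baseline of 3 are assumptions. Power at 40 v 40:

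| Reading of the effect | SD 0.5 | SD 1 | SD 2 |
|---|---|---|---|
| 0.14 HOMA-IR units | 24% | 9% | 6% |
| 14% of baseline 3 (0.14 × 3 = 0.42 units) | 96% | 46% | 15% |

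For 0.14 units, 80% power needs an SD of at most 0.14/0.634 = 0.22.

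**Step 4. What 80 patients can detect.** With 80% power, in SDs of the analysed variable and before baseline adjustment. The normal approximation is (1.96 + 0.8416)·√(2/n per side); the exact values use the noncentral t. Loss of 20% leaves 80 × 0.8 = 64.

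| Comparison | n per side | approximate | exact |
|---|---|---|---|
| Exercise main effect | 40 | 0.63 | 0.63 |
| Exercise main effect, after loss | 32 | 0.70 | 0.71 |
| Combination v one other group | 20 | 0.89 | 0.91 |
| Combination v one other group, after loss | 16 | 0.99 | 1.02 |

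The last two rows are before any Bonferroni correction. With three comparisons (alpha 0.0167) they become 1.06 and 1.20 SD.

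**Step 5. Gain from ANCOVA, on one scale.** In final-value SDs at 32 v 32, a change score detects 0.711·√(2(1−r)) and ANCOVA detects 0.711·√(1−r²). For an assumed baseline correlation r = 0.5 this is 0.71 against 0.62; for r = 0.7 it is 0.55 against 0.51.

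**The case against.** The strongest defence has four parts.

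- **The trial is labelled exploratory and disclaims power for interaction.** That is fair, and it tempers the consequences. It does not cover main effects, for which the same sentence claims adequate power, or the superiority hypothesis in section 2.1.
- **An article condenses the full protocol, which may hold the SD and a proper calculation.** A missing SD alone would not be a finding. Here, however, the article prints a model, its inputs and a conclusion, and these do not fit the endpoint or each other. An unseen document cannot make the printed calculation valid.
- **The inputs may be misprints.** The value 0.139 fits 5.3 million people better, and 14 percentage points comes close to the planned numbers. This may explain where the figure came from, but it remains a proportion test. For the same reason, the 53,000 shows that the inputs are incoherent; it is not the number of patients this trial needs.
- **Actual power may be sufficient.** This stands. A reader might infer that the trial is underpowered for its own stated effect. The document does not support that: it prints a percentage without a usable scale and gives no SD. Under a 14% reading with an assumed baseline of 3, power at 40 v 40 is 96% at SD 0.5.

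Two further cautions. Diabetes prevalence is the natural reading of 0.0139, but the article does not use that label. Post hoc power merely restates the p-value only if it is computed from the observed effect, and section 2.11 does not say which effect will be used.

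**Conclusion.** Wrong as written. A one-sample proportion model cannot size a between-group comparison of a continuous change, and the printed inputs do not yield 80 under any reading that keeps their sign and unit. The adequate-power claim is therefore unsupported. This conclusion needs no outside figure.

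It is not shown that power is inadequate. The range in Step 3, from 6% to 96%, depends entirely on assumed scales, SDs and a baseline, and illustrates only how much the text leaves open. What is firm is the detectable difference in SD units. The sample can support a claim about fairly large exercise effects, and only about still larger differences between the combination and any single group, which is the comparison the hypothesis names.

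**What to change.** 1. In section 2.2, delete the proportion model, the 0.0139 with its population count, and the −0.14%. Keep N = 80.
2. State instead what 80 patients can detect at two-sided alpha 0.05 and 80% power, in SDs of the analysed variable and before baseline adjustment. Give the Step 4 values for both the exercise main effect and the combination against each other group, with all 80 and after 20% loss, and say that the latter are before Bonferroni correction.
3. If a gain from ANCOVA is quoted, give both figures in final-value SDs with the assumed correlation, as in Step 5.
4. Remove the adequate-power claim for effects smaller than these.
5. In section 2.11, replace the post hoc power analysis with the 95% confidence interval of the exercise effect.

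The cost is rewording. The stated power becomes less favourable, and no patients are added.
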